### Dissemination of results

The trial protocol and results will be published in peer-reviewed journals. The results of the trial will be reported in accordance with the Consolidated Standards of Reporting Trials (CONSORT) Statement and its extension to non-pharmacological interventions [29, 30]. Participant-level datasets will be provided to researchers who are willing to perform meta-analysis by contacting the corresponding author.

## Discussion

The present study will test the hypothesis that RIPC performed during partial nephrectomy will reduce the IRI caused by renal artery clamping during surgery as well as the surgical insult. Our primary outcome variable will be serum creatinine value measured on the first postoperative day. However, as serum creatinine may be non-specific and insensitive to detect early subclinical renal injury, urinary biomarkers, as well as other secondary clinical outcomes, will be compared between groups. Our study should be able to give a reliable answer to the question of whether RIPC could protect the kidney from IRI during partial nephrectomy.

Patients who undergo partial nephrectomy are prone to develop postoperative renal parenchymal injury theoretically. Only a few studies reported the incidence of AKI after partial nephrectomy with currently available criteria including RIFLE (risk, injury, failure, loss of function, end-stage renal disease), the Acute Kidney Injury Network (AKIN) or Kidney Disease Improving Global Outcomes (KDIGO). To our knowledge, in two previous studies investigating the development of AKI in patients who underwent partial nephrectomy, the incidences of AKI were reported as 39% and 54% according to AKIN and RIFLE criteria, respectively [14, 31]. Another retrospective study attempting to identify the predictors of 30-day AKI after radical or partial nephrectomy reported that the incidence of AKI, defined as an elevation of serum creatinine > 2 mg/dl above baseline or the need for dialysis, was only 1.8% [32]. This low incidence may be due to the different definition of AKI and different inclusion criteria. Our study will add data about the incidence of AKI defined by KDIGO criteria after partial nephrectomy.

The protective effect of RIPC on vital organs against IRI has been reported in previous animal studies [33–36]. Remote ischemic conditioning provided widespread protection from IRI of the major organs including the liver, kidney, heart, and lung in animal models [34, 37]. As remote ischemic conditioning is a simple, inexpensive, and easily applicable technique in the clinical setting, efforts to translate this beneficial effect of RIPC in the animal studies into a clinical setting have been attempted. One clinical study suggested that remote ischemic preconditioning can prevent contrast medium-induced AKI in patients undergoing elective coronary angiography [38]. Ali et al. reported that RIPC reduced myocardial and renal injury after elective abdominal aortic aneurysm repair [39]. However, a recent multicenter trial with 1612 participants undergoing cardiac surgery reported no benefit of RIPC on the clinical outcomes including cardiac death, non-fatal myocardial infarction, coronary revascularization or stroke [2]. A recent Cochrane systemic review reported that there is no evidence that RIPC has a treatment effect on clinical outcomes. However, RIPC reduced cardiac troponin-T release measured at 72 h after surgery and expressed as area under the curve (AUC) [40]. Also, RIPC reduces the amount of cardiac troponin-I release measured at 48 and 72 h after surgery.

The optimal protocol and regimen of RIPC, including the timing, number of ischemia/reperfusion cycle and duration of each ischemic period, have not yet been established. Important variables in the regimen of RIPC are considered to be the optimal duration of the ischemia, the number of cycles repeated, and the site of application of the ischemia [41].

According to the Cochrane Review of ischemic preconditioning (IPC) for the reduction of renal IRI [8], the most common sites to which the IPC is applied are the upper and lower extremities, and three or four cycles of ischemia and reperfusion are used at 5-min intervals. As the muscle mass is different between upper and lower limb, the choice of the limb may influence the effect of RIPC. To provide enough ischemic insult to the limb to maximize the effect of RIPC, we decided to apply the four cycles of 5 min ischemia and 5 min reperfusion [42].

Our protocols have several limitations. First, urinary creatinine, microalbumin, β-2 microglobulin, and NAG were chosen as biomarkers of renal injury. These biomarkers were chosen because they are routinely measured in our clinical practice. However, there are other biomarkers with better performance such as urine tissue inhibitor of metalloproteinase-2 and insulin-like-growth-factor-binding protein 7 [50]. Measuring these biomarkers would enhance the sensitivity to detect and compare the renal injury. Second, although we will perform a randomized trial and adjust for the potential confounders in the multivariable analysis, the use of propofol as an induction agent may suppress the effect of RIPC on the renal dysfunction. Third, the sample size of our study was not calculated to detect a difference in the incidence of AKI, but a difference in serum creatinine level on the first postoperative day. Although a 0.35 mg/dl difference in serum creatinine is greater than a 0.3 mg/dl increase for defining stage 1 AKI in the KDIGO criteria [26], our sample size may not be sufficient to detect any difference in the risk of AKI.

In conclusion, our study protocol will test the effect of RIPC on the serum creatinine values after partial nephrectomy. Furthermore, our study will compare the incidence of AKI among the patients who received RIPC and those who did not. The urinary biomarker levels will help us to discriminate the degree of renal injury between the study groups more precisely. If the result of our trial supports our hypothesis, the next step in our research protocol will be to evaluate the long-term effect of RIPC in this surgical setting. Our patients will undergo ^99m^Tc-DTPA radionuclide scintigraphy to calculate GFR 6 and 12 months after surgery. This data will provide the long-term effect of RIPC in addition to the outcome variables that will be reported according to this study protocol.

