**Methods/design:**

We will conduct a randomized controlled trial enrolling the patients who will undergo partial nephrectomy. In the study group, RIPC which consisted of four 5-min cycles of limb ischemia and reperfusion will be conducted after induction of anesthesia. Postoperative serum creatinine values, the incidence of AKI, and urinary biomarkers, including urinary creatinine, microalbumin, β-2 microglobulin, and *N*-acetyl-beta-D-glucosaminidase, will be compared between groups during the postoperative 2 weeks. Regional oxygen saturation on the skin of the contralateral kidney will be measured to evaluate the association between intraoperative regional oxygen saturation values and renal injury of the operating side.

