**Discussion:**

We expect that our trial may demonstrate the effect of RIPC on mitigating the immediate postoperative renal injury and improving patient outcomes after partial nephrectomy. Moreover, our patients will undergo ^99m^Tc-DTPA radionuclide scintigraphy to calculate glomerular filtration rate 6 and 12 months after surgery. This data should show the long-term effect of RIPC.

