Theoretically, we assumed that RIPC, which can prevent IRI, may reduce renal ischemic injury in patients undergoing partial nephrectomy. There are only two randomized controlled trials (RCT) which evaluated the effect of RIPC during partial nephrectomy [15, 16]. Although these studies suggested the renal protective effect of RIPC, one study did not measure biomarkers to detect renal injury [15] and another study measured serum biomarkers of neutrophil gelatinase-associated lipocalin (NGAL) and cystatin C only during the immediate postoperative period [16]. However, as other urinary biomarkers, including urinary creatinine, microalbumin, β-2 microglobulin, and *N*-acetyl-beta-D-glucosaminidase (NAG) are also available [17–22], the effect of RIPC can be evaluated with these biomarkers. Glomerular filtration rate (GFR) and split function of each kidney can be measured by technetium diethylene triamine pentacetic acid (^99m^Tc-DTPA) radionuclide scintigraphy. Since AKI can predispose to chronic kidney disease [23], the long-term effect of RIPC in terms of GFR measured by scintigraphy need to be evaluated.

Therefore, we hypothesized that RIPC may mitigate the IRI due to renal arterial clamping during partial nephrectomy, thereby, reducing the elevation in serum creatinine and urinary biomarkers of renal injury. We aimed to evaluate the effect of RIPC on postoperative renal function measured by serum creatinine, urinary biomarkers, and GFR measured by scintigraphy.

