**Fig. 2 Fig2:**
[figure not shown]
Flow diagram of measurements in the study. *sCr* serum creatinine, *eGFR* estimated glomerular filtration rate, *Hb* hemoglobin, *RIPC* remote ischemic preconditioning, *I*  ischemia, *R*  reperfusion, *rSO*_*2*_ regional oxygen saturation, *PACU* post-anesthesia care unit. Urinary biomarkers, including urinary creatinine, microalbumin, β-2 microglobulin, and *N*-acetyl-beta-D-glucosaminidase will be measured

Also, GFR measured by ^99m^Tc-DTPA renal scintigraphy will be obtained for a preoperative baseline and at 6 and 12 months after surgery.

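### Scintigraphic GFR at 6 and 12 months is an unconditional aim and endpoint in three places, but the Discussion ties evaluation of the long-term effect to a supportive result

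*Protocol article*

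**What the plan says.** Three parts of the protocol article treat scintigraphic GFR as belonging to this trial, with no condition attached.

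- **Background.** The authors argue that "the long-term effect of RIPC in terms of GFR measured by scintigraphy need to be evaluated". Their aim then names it as one of three measures: "We aimed to evaluate the effect of RIPC on postoperative renal function measured by serum creatinine, urinary biomarkers, and GFR measured by scintigraphy".
- **Study endpoints** (text after the Fig. 2 legend). GFR by "renal scintigraphy will be obtained for a preoperative baseline and at 6 and 12 months after surgery". It carries neither a primary nor a secondary label.
- **Abstract, Discussion paragraph.** After announcing the 6- and 12-month scans it says: "This data should show the long-term effect of RIPC".

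The last paragraph of the main Discussion reads differently. It says: "If the result of our trial supports our hypothesis, the next step in our research protocol will be to evaluate the long-term effect". It next repeats, without condition, that the patients will have the scans, and closes: "This data will provide the long-term effect of RIPC in addition to the outcome variables that will be reported according to this study protocol".

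The Statistical analysis section lists serum creatinine, eGFR, urinary biomarkers and contralateral rSO2 for repeated-measures analysis of variance. Scintigraphic GFR is not on that list. The same section also gives a general rule for continuous outcome variables: a t test or a Mann-Whitney test between the two groups.

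**The concern.** If the Discussion sentence is followed as written, whether a stated aim is evaluated depends on how the early outcomes turn out. Long-term GFR would then tend to be reported when the early result favours RIPC and might go unreported when it does not. A reader of the published 12-month data could not tell whether they appeared because they were planned or because the first result was encouraging.

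What is at stake is the credibility of the long-term evidence. The day-1 creatinine comparison is not affected.

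**Working it through.** This is a question of text. The plan's only design calculation (39 patients per group before dropout, 43 after) concerns day-1 creatinine and has no bearing here. The check sets the statements side by side.

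1. **Is scintigraphic GFR part of this trial?** Yes. It is in the aim (Background), under Study endpoints, and in the Abstract.

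2. **Is taking the scans conditional?** No. Study endpoints, the Abstract and the last paragraph of the Discussion all say that they will be done.

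3. **Is evaluating them conditional?** In one place, yes. The sentence quoted first from the Discussion opens with a condition on the result. The hypothesis it refers to is set out in the Background as a smaller rise in serum creatinine and urinary biomarkers. The condition is therefore on the early outcomes, and the primary one is day-1 creatinine.

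4. **Does the next step mean a different study?** Not on a plain reading. The following sentence concerns this trial's own patients and the same 6- and 12-month scans.

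5. **Are the data among the outcomes to be reported?** The Discussion calls them "in addition to the outcome variables that will be reported according to this study protocol". The Abstract's Methods paragraph says that the creatinine, AKI and biomarker outcomes "will be compared between groups during the postoperative 2 weeks". The two statements together separate the long-term GFR from the main report. They do not say that it will go unreported.

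6. **Could the condition operate in practice?** Each patient's primary outcome is known on day 1 and the last scan comes at 12 months. Trial status expects enrolment to finish in winter 2018, so the last scans fall about a year later. The Randomization section keeps allocation undisclosed until the end of the study. If that end were the last 12-month scan, group results would not be known beforehand. The next-step wording suggests instead that the early result comes first.

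7. **Does the analysis section settle it?** Only in part. The repeated-measures list omits this endpoint. The general two-group tests can cover it, since it is a continuous variable under Study endpoints. Those tests make no use of the preoperative scan, although it is collected in every patient. With correlation ρ between the preoperative and follow-up values, baseline adjustment reduces the residual variance to about (1 − ρ²) of the unadjusted variance. The documents give no ρ, so the gain cannot be stated.

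Result: steps 1 and 2 conflict with step 3, and step 5 leaves unclear where and when the data will be reported.

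**The case against.** The best defence is that the sentence is Discussion prose about a research programme and is neither an analysis rule nor a reporting rule. The sentences after it are unconditional, and the closing phrase fits a planned later paper: the other outcomes end at 2 weeks and the scans at 12 months. Staged reporting is not selective reporting.

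Much of this stands, and it rules out several stronger readings that a reader might infer:

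- **That a negative trial would drop the long-term data.** The text does not say what follows a negative result, and the scans go ahead regardless.
- **That no comparison applies to this endpoint.** The general two-group tests in the Statistical analysis section can cover it. What is missing is its name and any baseline adjustment.
- **That scintigraphic GFR is the better test of the hypothesis.** The hypothesis concerns acute change, and the Discussion's remark on creatinine's insensitivity is about early subclinical injury. A 12-month scan does not address that; it addresses whether an effect lasts.
- **That operated-kidney GFR would give a known gain in power over total GFR.** Eligibility puts the contralateral share above 40%, so the operated kidney supplies less than 60% of function, and an effect confined to it is diluted in the total. The documents give neither an expected effect nor the variability of split GFR, so no gain can be computed.

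The defence does not remove the conflict itself. The aim says that scintigraphic GFR will be evaluated; the Discussion says that the long-term effect will be evaluated next if the result is supportive. Condensing a full protocol into an article can explain omissions, but it does not explain two incompatible statements within one article.

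**Conclusion.** The point holds as an internal contradiction. An aim and endpoint stated without condition in the Background, Study endpoints and Abstract becomes, in the last paragraph of the Discussion, a follow-on whose evaluation is tied to a supportive result and whose data lie apart from the main report. That leaves the endpoint open to result-dependent reporting. It is a risk arising from the wording and is no evidence of intent.

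Its size is modest. One endpoint, measured at two follow-up times, is affected; the primary analysis and the sample size are not. No bias can be quantified from the documents. The conclusion assumes that the condition refers to this trial's early outcomes and this cohort, which is the natural reading of the paragraph.

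**What to change.** 1. Delete the conditional sentence in the last paragraph of the Discussion, or reconcile it with the Background, Study endpoints and Abstract.
2. Under Study endpoints, label scintigraphic GFR at 6 and 12 months as a secondary outcome. State that it will be analysed and reported whatever the day-1 creatinine result, in a later report if need be.
3. In the Statistical analysis section, name the comparison: ANCOVA of GFR at each time on group and preoperative scintigraphic GFR, in all randomised patients, with missing scans handled by the multiple imputation already planned. Restricting it to patients with a scan would depart from that plan.
4. Optionally, report operated-kidney (split) GFR beside total GFR, since the scan already provides it.

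The cost is wording in the protocol and analysis plan. The baseline, 6-month and 12-month scans are already scheduled, so no extra patients, visits or measurements are needed. The change is most credible if it is dated before group results are known.

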## Trial status

The study was initiated in September 2017. By June 2018, 46 patients had been enrolled in this study. Enrollment of 86 patients is expected to be completed in the winter of 2018.

## Abbreviations

^99m^Tc-DTPA: Technetium diethylene triamine pentacetic acid
AKI: Acute kidney injury
AKIN: Acute Kidney Injury Network
eGFR: Estimated glomerular filtration rate
IRI: Ischemia-reperfusion injury
KDIGO: Kidney Disease Improving Global Outcomes
NAG: *N*-acetyl-beta-D-glucosaminidase
NGAL: Neutrophil gelatinase-associated lipocalin
NIRS: Near-infrared spectroscopy
RIPC: Remote ischemic preconditioning
rSO_2_: Regional oxygen saturation
